### The intervention

#### Prescription of walking intervention

The walking intervention will be conducted in duration of 16 weeks, with 3 sessions per week and 50–70 min per session. As respects to the culture of KSA, male and female participants will undergo intervention in separate groups, with supervision or assistance by professional trainers or research assistants in the same gender during the intervention. In intervention program, the ACSM progressive training principle will be adopted. The intensity and repetition will be progressively increased in accordance with the 4 levels as prescribed, in which weeks 1 to 4 are Level-1; weeks 5 to 8 are Level-2, weeks 9 to 12 are Level-3, weeks 13–16 are Level-4 (Please refer to Table 1 for the detailed intervention program). The levels of progression could ensure the physically inactive participants have sufficient time to equip with an appropriate base of fitness and familiar with regular walking regime, as well as to prevent musculoskeletal injuries and over training. Also, the design of the training sessions will include the expected target heart rates, the intensity and the expected number of steps. Most importantly, each participant will be required to put on a wrist-worn Fitbit Charge 3 to keep track of their exercise intensity levels, including their heart rate changes in relation to their target heart rate zones, and the accumulated amount of steps after each session. In addition to progression, the training principle of individuality will also be applied to the participants doing the walking. They will be allowed to complete the targeted steps based on their own targeted heart rates as well as physical conditions during walking. Participants are free to taking short breaks or withdraw from walking if they uncomfortable doing it according to the schedule. Furthermore, in order to minimize the external influences caused by environmental settings, both intervention groups will receive the training at the same indoor track/sports paradise, with air-conditioning to produce a constant temperature.

**Table 1 Tab1:** Intervention Protocol (Coswig et al., 2020 ; Harris et al., 2017; Haynes et al., 2020; Ignaszewski et al., 2017;Tudor-Locke et al., 2018)

Intervention Group	SGBI	NSIBI

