Additionally, to respect the culture of KSA, male and female participants will be separated to undergo the walking intervention. In such arrangement, there will be 4 groups [2 groups (1 male and 1 female) under group-based and 2 groups (1 male and 1 female) under individual-based] and each group will have 21 participants when doing walking. While qualified professional fitness trainers (1 male and 1 female separately for male and female groups, respectively) will be involved in the group-based intervention programs in order to provide appropriate guidance and supervision to the participants. Whereas, the non-supervised individual-based intervention will be conducted by a research assistant (males and females) to ensure the attendance and general safety, but without providing professional advice or supervision.

Upon completion of the 16-week walking interventions, only data of the participants who have attended at least 70% of the training sessions will be included in the analyses.

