### The control group

Participants in the control group (CG) (21 males and 21 females) will not participate in any specific intervention during the whole study period (the 16-week intervention and 12-week follow-up periods), but they will be asked to keep a daily log of their physical activity, use of medicines, illness, and other health-related activities. In addition, the CG participants will be asked to report to the research assistant (RA) if a major change has been made in the aforementioned aspects. The RA will also check the daily logs of the participants through a telephone or mobile phone every two weeks. Data from those who had changed their normal lifestyles (especially taking up regular physical activity) will be examined for exclusion in the subsequent data analysis.

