### Statistical analysis

Descriptive statistics will be used to describe baseline characteristics such as gender, age, living status (alone or with family), body height, body weight, resting heart rate, and blood pressure of the participants in the study. The primary outcomes will be analyzed using an intention-to-treat (ITT) approach, and a sensitivity test will subsequently be conducted using the available data. Missing data will be replaced using the last observation carried forward method. For the secondary outcomes, a per-protocol analysis will be conducted using the available data. The statistical significance level was set at *p* < .05. All data will be analyzed using SPSS Version 26.0 (IBM, Chicago, IL). For the within-group test, a one-way repeated measure analysis of variance (ANOVA) will be applied to each group to determine the changes of each outcome parameter among the three-time points (i.e., pretest, posttest, and follow-up test). When the sphericity assumption was violated, the Greenhouse– Geisser correction will be used when epsilon < 0.75, or the Huynh–Feldt correction will be used when epsilon > 0.75. Post hoc analysis with Bonferroni correction will be conducted to explore the differences between the pretest and posttest, as well as posttest and follow-up test. The mean differences with 95% confidence intervals (CIs) will be reported. For the inter-group test, a one-way analysis of covariance (ANCOVA) with the baseline value as a covariate will be conducted at the posttest, and follow-up test to determine the group effect on each outcome parameter. Subsequently, the differences between the intervention groups and the control group will be analyzed through planned contrasts.

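### The unqualified 70% attendance rule, and a discretionary exclusion of controls who change lifestyle, conflict with the intention-to-treat analysis stated for the primary outcomes.

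*Protocol article*

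**What the plan says.** Four statements in the protocol article decide who is analysed.

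- **Prescription of walking intervention** (closing paragraph, after Table 1): on completion of the 16 weeks, "only data of the participants who have attended at least 70% of the training sessions will be included in the analyses". No outcome or analysis is exempted. The programme is "conducted in duration of 16 weeks, with 3 sessions per week".
- **The control group**: "Data from those who had changed their normal lifestyles (especially taking up regular physical activity) will be examined for exclusion". No threshold is given, and nothing says which analysis is meant.
- **Statistical analysis**, primary outcomes: "The primary outcomes will be analyzed using an intention-to-treat (ITT) approach", followed by a sensitivity test on available data. "Missing data will be replaced using the last observation carried forward method".
- **Statistical analysis**, secondary outcomes: "For the secondary outcomes, a per-protocol analysis will be conducted using the available data". The per-protocol set is not defined there.

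**The concern.** An analysis limited to participants who reached an attendance threshold is not intention-to-treat. For the primary outcomes, an analyst who follows the attendance sentence as written departs from the Statistical analysis section, and the reverse.

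Three features make this more than untidy wording.

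- Attendance and lifestyle change both arise after randomisation, so selecting on them gives up the comparability that randomisation provides.
- The rules differ by arm. Attendance can only apply to walkers, and lifestyle change is applied only to controls.
- Attendance is part of what the trial compares. The section on the design of the intervention programs cites a meta-analysis in which supervised group exercise did better on adherence as well as on quality of life. Filtering on attendance would remove part of that difference and would select differently in the two walking arms, which are the main comparison.

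Until the text is reconciled, the primary analysis set remains open to a choice made after the data are seen.

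**Working it through.** **1. What the rule means in sessions.** 16 weeks × 3 sessions = 48. 70% of 48 = 33.6, so at least 34 sessions are needed. At three sessions a week, 34 sessions cannot be reached before week 12 (11 × 3 = 33). Anyone who leaves before then is excluded, whatever the reason. Carrying the last observation forward would then have little left to do for early leavers in the walking arms, although the plan provides it for the primary outcomes.

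**2. The sections side by side, for the primary outcomes.**

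| Section | Who is analysed |
|---|---|
| Statistical analysis | All randomised (intention-to-treat), missing values carried forward |
| Prescription of walking intervention | Only those with at least 34 of 48 sessions |
| The control group | Controls, less any excluded on judgement for lifestyle change |

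The first row cannot be combined with the second if the second applies to the primary outcomes, and nothing in the article says that it does not. Read literally, the attendance rule would also remove every control, since controls have no sessions; it is presumably meant for walkers only.

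**3. Illustrative size.** The document gives no figure for this point, so these inputs are assumptions: a share q of walkers excluded (20% or 30%), and a correlation r of 0.2 to 0.4 between attendance and the baseline-adjusted outcome. The 20% equals the dropout allowance under Sample size estimation, but it is not a stated attendance figure. With no treatment effect, and φ the normal density at the q-quantile z:

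shift = r × λ, where λ = φ(z)/(1 − q)

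- q = 0.20: λ = 0.280/0.80 = 0.350
- q = 0.30: λ = 0.348/0.70 = 0.497

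The two-sided type I error compares one filtered walking arm, with n₁ left of 42, against 42 controls:

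SE = √(v/n₁ + 1/42), v = 1 − r²λ(λ − z)

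error = Φ(−1.96 − shift/SE) + 1 − Φ(1.96 − shift/SE)

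| q | n₁ | r | shift (SD) | type I error |
|---|---|---|---|---|
| 0.20 | 34 | 0.2 | 0.07 | 6.1% |
| 0.20 | 34 | 0.3 | 0.11 | 7.5% |
| 0.20 | 34 | 0.4 | 0.14 | 9.5% |
| 0.30 | 29 | 0.2 | 0.10 | 7.0% |
| 0.30 | 29 | 0.3 | 0.15 | 9.6% |
| 0.30 | 29 | 0.4 | 0.20 | 13.5% |

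If the most improved 10–20% of controls were also excluded, with r = 0.2–0.3 in both arms, the shift would be 0.11–0.25 SD and the type I error 7.5–17.7%.

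**4. Between the two walking arms.** With 10% excluded in one arm and 30% in the other, λ is 0.195 and 0.497, a difference of 0.302. Times r = 0.2–0.4, this is 0.06–0.12 SD. Its sign depends on which arm loses more people.

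**5. Scale.** The planned effect is 0.25 with no metric named. Reading it as Cohen's f is supported by the sample size: a between-groups repeated-measures calculation with three groups, three time points and an assumed within-person correlation of 0.5 gives 108 in total, and power 0.797 at the stated 105. With three equal arms, f = 0.25 implies a largest pairwise difference of 0.25 × 3/√2 = 0.53 SD (two arms equal) to 0.25 × √6 = 0.61 SD (evenly spaced).

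**The case against.** The best defence is that the sections can be read together. The Statistical analysis section assigns intention-to-treat to the primary outcomes and per-protocol to the secondary ones without defining the latter set. The attendance and lifestyle rules are the only candidate definition, and if that is what they are, nothing conflicts and only a qualifier is missing. This may well be the intention. It does not remove the point: the attendance sentence says only, refers to the analyses in general, and carries no such qualifier.

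Several stronger readings are tempting, and the documents do not support them.

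- *That controls who became active will be removed.* The text says that their data "will be examined for exclusion in the subsequent data analysis". This is possible and discretionary, not automatic. The weakness is the missing criterion.
- *That per-protocol analysis of the secondary outcomes contradicts the plan.* It is openly planned. One may prefer to see an all-randomised analysis beside it, but that is a methodological preference.
- *That every secondary outcome could be analysed in all randomised participants.* Walking performance is recorded per training session, so it does not exist for controls or for missed sessions. Enjoyment is measured after taking part in a walking programme, so a three-arm analysis is doubtful there too.
- *That low attenders are not assessed.* No section says so. The voucher terms under Participants list completed assessments and 70% attendance as separate conditions, which suggests that assessment does not depend on attendance.
- *That the bias must favour walking.* This needs a positive link between attendance and outcome. Control logs also cover illness and medicines, and the exclusion names activity especially, not solely. Excluding controls whose health worsened would push the other way.

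The planned ANCOVA also adjusts for the baseline score, so selection acting through baseline is largely dealt with. Only the correlation with the baseline-adjusted outcome matters; if r is taken for the raw score, the illustration overstates the bias.

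**Conclusion.** The point holds for the primary outcomes. The attendance rule is stated without limit and is incompatible with the intention-to-treat analysis if applied there. The control-group rule adds a second, less firm departure because it is discretionary and has no criterion. Both would select on behaviour after randomisation, differently by arm.

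The bias probably favours walking over control, but neither direction nor size is established. The shift of 0.07–0.20 SD for the attendance rule alone rests wholly on the assumed 20–30% exclusion and correlation of 0.2–0.4 with the baseline-adjusted outcome. Against a planned difference of roughly 0.53–0.61 SD, itself dependent on reading 0.25 as Cohen's f, that would not be negligible. The comparison is rough, because the shift is in SDs of the adjusted outcome. The conflict itself depends on none of these figures.

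**What to change.** - **Prescription of walking intervention and The control group:** state that these exclusions do not apply to the primary-outcome analysis, which includes all randomised participants in their allocated arm.
- **Per-protocol set:** use the 70% rule (34 of 48 sessions, walking arms only), together with a control criterion fixed in advance and applied blind to outcome, solely to define a labelled per-protocol or sensitivity analysis.
- **Secondary outcomes:** for those measured in all arms at all three time points (body composition, resting heart rate, resting blood pressure), add an all-randomised analysis beside the planned per-protocol one. Leave per-session walking performance as it is.

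The cost is wording in three sections and a few extra analyses of data already planned. The small downside is a possibly more diluted estimate, since low attenders stay in. Retaining all 126 does not in itself cost power: with complete data, f = 0.25 and an assumed within-person correlation of 0.5, the calculation used above gives 0.87 at 126 against 0.797 at 105, before any dilution.

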### The control group

Participants in the control group (CG) (21 males and 21 females) will not participate in any specific intervention during the whole study period (the 16-week intervention and 12-week follow-up periods), but they will be asked to keep a daily log of their physical activity, use of medicines, illness, and other health-related activities. In addition, the CG participants will be asked to report to the research assistant (RA) if a major change has been made in the aforementioned aspects. The RA will also check the daily logs of the participants through a telephone or mobile phone every two weeks. Data from those who had changed their normal lifestyles (especially taking up regular physical activity) will be examined for exclusion in the subsequent data analysis.

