### Intervention experience evaluation

To further investigate and compare the perception of the participants after the intervention, a few open-ended questions regarding their feelings and attitude towards the intervention, as well as their physical activity behavior after the intervention will be asked in the follow-up test. (Please refer to Appendix for the examples of the questionnaire items)

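### Medicines, illness and outside activity are logged and checked every two weeks in the control arm only, so these changes can be seen, and lead to exclusion, in one arm of three

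*Protocol article*

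**What the plan says.** The section on the control group sets three duties for that arm. Participants are asked to keep a record: "they will be asked to keep a daily log of their physical activity, use of medicines, illness, and other health-related activities". They must also volunteer changes: "the CG participants will be asked to report to the research assistant (RA) if a major change has been made in the aforementioned aspects". The record is then followed up: "The RA will also check the daily logs of the participants through a telephone or mobile phone every two weeks". The section describes the controls' status "during the whole study period (the 16-week intervention and 12-week follow-up periods"), that is, through intervention and follow-up. It also gives the use of the data: "Data from those who had changed their normal lifestyles (especially taking up regular physical activity) will be examined for exclusion in the subsequent data analysis".

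For the walking arms, the intervention section and its table describe sessions, staffing, target heart rates and step counts. The Fitbit supplies heart rate, steps and time for each session. Trainers supervise the group arm. In the individual arm a research assistant is present "to ensure the attendance and general safety, but without providing professional advice or supervision". After week 16 the article describes open-ended questions on feelings and attitudes towards the intervention, "as well as their physical activity behavior after the intervention will be asked in the follow-up test". It assigns no log of medicines, illness or outside activity, and no two-weekly check, to either walking arm.

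Resting heart rate and resting blood pressure are secondary outcomes, measured at pretest, posttest and follow-up. The residual effect 12 weeks after the programme is a stated aim.

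**The concern.** The arms are compared on outcomes that respond to things happening outside the programme. A change in blood-pressure or heart-rate medicine can move resting blood pressure and resting heart rate. Continued or additional activity can move most outcomes at the 12-week follow-up. The protocol collects these facts prospectively in one arm and not in the other two.

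Three things are at stake:

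- **Resting blood pressure and heart rate.** A medicine change in a control can be seen. In a walker it cannot, and may be read as an effect of walking.
- **Residual effect.** Activity in weeks 17–28 is recorded daily in controls and recalled once by walkers, so a lasting effect of the programme and continued walking cannot be told apart on comparable data.
- **Handling in analysis.** Controls whose log shows a changed lifestyle may be dropped, and walkers with the same change cannot be found. The walking arms have their own exclusion rule, 70% attendance, but it concerns sessions attended and not outside behaviour. The statistical analysis section promises intention-to-treat for the primary outcomes, and log-based exclusion in one arm sits badly with that.

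The logs also contain illness. The article names a risk of the programme when it explains the graded progression ("as well as to prevent musculoskeletal injuries and over training"), so a later reader may be tempted to tabulate illness by arm from them.

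**Working it through.** The plan gives no figure on this point to reproduce. The check sets out what is collected in each arm, and then asks what can be said about bias.

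**Inputs from the article:** 16 intervention weeks; 12 follow-up weeks; log check every 2 weeks (control); 3 sessions a week (walking); 42 participants per arm.

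**Collection per participant**

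| | Control | Each walking arm |
|---|---|---|
| Log days | (16 + 12) × 7 = 196 | 0 described |
| Two-weekly checks, weeks 1–16 | 16 / 2 = 8 | 0 described |
| Two-weekly checks, follow-up | 12 / 2 = 6 | 0 described |
| Total checks | 8 + 6 = 14 | 0 described |
| Staffed sessions, weeks 1–16 | 0 | up to 16 × 3 = 48 |
| Activity after week 16 | daily log | one set of open-ended questions |

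**Blood pressure and heart rate.** Let p_W and p_C be the shares of walkers and controls who change a relevant medicine, and d the mean effect of such a change on the outcome. Medicine changes then contribute (p_W − p_C) × d to the difference between arms. Unequal logging does not itself create this term. It leaves p_W unknown, so nobody can check whether the term is near zero. The article gives no value for p_W, p_C or d, so no size can be calculated.

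**Illness or harms, if the logs were used for this.** Apparent risk ratio = true risk ratio × (share captured in walkers / share captured in controls). The capture shares below are assumptions, since the article gives none.

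| Captured, walkers | Captured, controls | Ratio of shares | True RR 1.0 appears as | True RR 2.0 appears as |
|---|---|---|---|---|
| 90% | 90% | 1.00 | 1.00 | 2.00 |
| 70% | 90% | 0.78 | 0.78 | 1.56 |
| 50% | 90% | 0.56 | 0.56 | 1.11 |
| 30% | 90% | 0.33 | 0.33 | 0.67 |
| 90% | 60% | 1.50 | 1.50 | 3.00 |

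The last row is included because staff see walkers up to 48 times in weeks 1–16, while controls have 8 checks. Capture in that period could be higher in walkers for events that occur at sessions. The table shows that unequal capture would distort the comparison. It does not show by how much or in which direction.

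**The case against.** The strongest defence is that the log is a contamination check on an untreated arm. The article says so: its stated purpose is to find controls who took up activity. Walkers are monitored in another way, by attendance, Fitbit and staff at every session. On this view the arms have different logs because they have different risks of departing from plan. That explains why the log was written for controls. It does not explain why medicines and illness are logged in one arm only, and it does not cover the follow-up period, when walkers have no sessions.

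It may also be said that a journal article condenses, and that the full protocol may give walkers a log. That is possible. But the article describes both walking arms in detail and places the log, the duty to report and the check under the control group. The sentence on checking speaks of participants in general, but it stands in that section and refers to those logs.

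A reader might infer more: that exercise harms go unrecorded in the walking arms, and that any comparison of harms is biased in favour of walking. The document does not support this. It states no harms outcome and no harms comparison. Adverse-event recording may sit in the full protocol, and staff attend the sessions. A comparison based on separate and equal collection would be unaffected.

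Nor does it hold that self-monitoring and contact are given to controls alone. Walkers wear a Fitbit against heart-rate and step targets and meet staff far more often.

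Two further qualifications stand. The article's remark that hypertension is prevalent concerns older Saudi adults in general, while the trial enrols healthy, independent people. And continued walking by walkers may be counted as part of the residual effect, which is a reason to record it rather than to exclude anyone for it.

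**Conclusion.** The point holds in a limited form. As written, medicine changes, illness and outside activity are recorded prospectively and checked in the control arm only, over 28 weeks: 196 log days and 14 checks per control, with no equivalent described for the 84 walkers. This weakens the interpretation of resting blood pressure, resting heart rate and the 12-week residual effect, and it allows exclusion for lifestyle change in one arm only. The gap is widest in the 12-week follow-up, where the article describes no contact with walkers between the posttest and the follow-up test.

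The size and direction of any bias are unknown, because the article gives no rate of medicine change, outside activity or event capture. The conclusion assumes that the full protocol gives walkers no matching log. It is worth correcting before data collection, because events that nobody recorded cannot be recovered reliably afterwards.

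**What to change.** Give all three arms the same log, covering illness, injury, medicine changes and activity outside the sessions, for the full 28 weeks and on the same two-week cycle. State this in both the intervention and control-group sections.

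- **Weeks 1–16:** the research assistant already at the sessions collects the log from walkers at one session every two weeks. Controls keep the telephone check.
- **Follow-up:** the same telephone check in every arm. Added work: 12 / 2 = 6 calls × (42 + 42) = 84 walkers = 504 short calls over 12 weeks.
- **Lighter alternative:** keep the log in all arms and drop the calls in all arms alike.
- **Analysis:** summarise the log by arm for all randomised participants. Do not use a control-only log for exclusions or for any comparison of illness.

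The cost is an existing form given to 84 more people, some participant burden and research-assistant time. Sample size, outcomes and visit schedule do not change. Because the calls would reveal group allocation if they differed by arm, a common script in follow-up also helps to keep staff contact alike.
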